### Potential Drug Interactions

Medscape interaction checker calculator application would be used for checking potential drug interactions each visit . The drugs having significant interactions would be substituted unless the risk of using the medicine concurrently exceeds the benefit.

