### General Concomitant Medications and Supportive Care Guidelines

1. Loperamide for patients with Grade II or more diarrhoea following chemotherapy.
2. Doxycycline for patients with Grade II or more rash following chemotherapy
3. Topical steroids for patients with Grade II or more rash following chemotherapy
4. Oral steroid for patients with Grade II or more nausea or vomiting following weekly methotrexate

5. Antibiotics can be administered to patients presenting with febrile neutropenia as per the institute antibiotic policy.
6. Patients should continue pre-existing medications for other comorbid conditions. However the same should be noted for any significant interactions.

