## **21 Harms**

An adverse event will be defined as any untoward medical occurrence in a subject without regard to the possibility of a causal relationship. Adverse events will be collected after the subject has provided consent and enrolled in the study. If a subject experiences an adverse event after the informed consent document is signed (entry) but the subject has not started to receive study intervention, the event will be reported as not related to study drug. All adverse events occurring after entry into the study and until hospital discharge will be recorded. An adverse event that meets the criteria for a serious adverse event (SAE) between study enrollment and hospital discharge will be reported to the local IRB [institutional review board] as an SAE.

If chemotherapy is discontinued as a result of SAE, study personnel will document the circumstances and data leading to discontinuation of treatment. A serious adverse event for this study is any untoward medical occurrence that is believed by the investigators to be causally related to study-drug and results in any of the following: Life-threatening condition (that is, immediate risk of death); severe or permanent disability, prolonged hospitalization, or a significant hazard as determined by the data safety monitoring board. Serious adverse events occurring after a subject is discontinued from the study will NOT be reported unless the investigators feels that the event may have been caused by the study drug or a protocol procedure. Investigators will determine relatedness of an event to study drug based on a temporal relationship to the study drug, as well as whether the event is unexpected or unexplained given the subject's clinical course, previous medical conditions, and concomitant medications.

The study will monitor the following adverse events during chemotherapy cycles:

Haematological

Anemia

Leucopenia

Thrombocytopenia

Febrile neutropenia

Non hematological

Nausea

Vomiting

Oral mucositis

Pain

Xerostomia

Dysphagia

Dyspnea

Anorexia

Diarrhea

Constipation

Dysgeusia

Fatigue

Peripheral Sensory neuropathy

Peripheral Motor Neuropathy

Nail infection

Weight loss

Myalgia

Joint Pain

Alopecia

Biochemical

Increase in serum creatinine

Increase in Alanine Aminotransferase (SGPT)

Increase in Alkaline Phosphatase (ALP)

Increase in Bilirubin

Decrease in serum albumin (Hypoalbuminemia)

Increase or decrease in Serum electrolytes

Sodium

Potassium

Corrected Calcium

Magnesium

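### The drug-interaction rule transposes risk and benefit, so the duty to substitute lapses exactly when concurrent use does net harm (minor wording error)

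*Protocol*

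**What the plan says.** The rule stands in the protocol, section 11.4, under Potential Drug Interactions, which consists of two sentences. The first sets the check: "Medscape interaction checker calculator application would be used for checking potential drug interactions each visit". The second sets the action: "The drugs having significant interactions would be substituted unless the risk of using the medicine concurrently exceeds the benefit".

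Two other places in the protocol touch on co-medication:

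- Section 11.2, General Concomitant Medications and Supportive Care Guidelines, item 6, has patients stay on the medicines they already take for other conditions and adds: "However the same should be noted for any significant interactions". It names no action beyond noting.
- Section 21, Harms, lists "previous medical conditions, and concomitant medications" among the things an investigator weighs when deciding whether an adverse event is related to study drug. That is attribution after an event and says nothing about managing an interaction.

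**The concern.** A rule of this kind normally replaces an interacting drug by default and allows it to be kept when its benefit justifies the risk. Here the exception is tied to the opposite condition. The safeguard is withdrawn for net-harmful combinations and kept for combinations whose benefit is at least as great as their risk.

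The sentence is an operative instruction: it is the only action step attached to a safety check made at every visit. The protocol itself treats the pharmacology of this regimen as consequential. Section 4.4 describes transporters that clear methotrexate from the cell and erlotinib's inhibition of one of them, and section 10.2 (item 7) excludes patients with QTc prolongation because of a cardiac risk linked to celecoxib. Avoidable toxicity also has a direct cost to the patient, because under section 11.3 (item 3) toxicity that stops one or more of the agents ends protocol treatment.

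**Working it through.** No figure is involved, so the check is a logical reading of the sentence followed by a search for any text that corrects it.

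**Step 1: the form of the rule.** The default is to substitute the interacting drug. The exception is that the risk of concurrent use is greater than its benefit. Substitution is therefore required when risk ≤ benefit, and not required when risk > benefit.

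**Step 2: the three cases.**

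| Balance for concurrent use | Rule as written | Rule with the nouns swapped |
|---|---|---|
| Risk > benefit | Substitution not required | Substitute |
| Risk = benefit | Substitute | Substitute |
| Benefit > risk | Substitute | May be kept |

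The two versions agree only at the tie. Of the two cases that differ, only the first is a safety concern. In the last, the written rule is merely over-cautious.

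**Step 3: can another reading rescue it?**

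- The clause could be taken to mean the risk of making the substitution. It cannot, because it names the risk of using the medicine concurrently.
- It could be taken to mean that the drug is stopped outright when the risk is too high. The subsection names no action other than substitution.
- The text could be damaged. It is intact running prose, with no table, gap or redaction.

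**Step 4: does other text correct it?**

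| Place in the protocol | Mentions co-medication interactions | Sets an action on them | Right direction |
|---|---|---|---|
| Section 11.4, Potential Drug Interactions | Yes | Yes | No |
| Section 11.2, item 6 | Yes | No (noting only) | Not applicable |
| Section 21, Harms | No (attribution only) | No | Not applicable |

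Two places mention such interactions, one sets an action, and none states it correctly. For a pre-existing medicine, once section 11.4 lifts the default, the remaining instruction is the one in section 11.2 to carry on with it and note the interaction.

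**The case against.** The strongest reply is that the intent is obvious. A check at every visit, with substitution as the default, makes no sense if its only exception is for harmful combinations, so a clinician would read the sentence the right way round. Lifting a default is also not an order to continue: nothing in the subsection forbids stopping or replacing a harmful co-medication.

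Other provisions limit the effect too:

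- Section 10.2 excludes patients on methotrexate for other indications, long-term COX-2 inhibitor users and patients with QTc prolongation.
- Section 11.4 sets blood count, renal and liver monitoring with dose rules.
- Section 11.3 (item 6) lets the investigator take a patient off treatment.
- Sections 20.1 and 22 provide data monitoring board oversight and six-monthly audit.

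All of this stands as a reason to keep the rating low. None of it makes the sentence correct. The exclusions cover only a few specific situations, the laboratory rules respond after exposure, removal under section 11.3 deals with the trial treatment and not the co-medication, and oversight and audit do not restate the rule. An audit against the written text would be checking the reversed rule.

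**Conclusion.** The sentence is wrong as written, and the error is minor. It looks like a drafting slip and not a deliberate choice. It bears on patient safety only, and only where an interacting co-medication carries more risk than benefit and the text is followed literally.

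How often that would happen cannot be estimated, because the protocol gives no frequency of interacting co-medication. No effect on sample size, error rates, the primary analysis or the PK-PD model is claimed. That the reversal is plain on the face of the text and corrected nowhere else is not in doubt. The low rating rests on the judgement that most clinicians would see what was meant.

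**What to change.** In section 11.4, Potential Drug Interactions, second sentence, exchange the words risk and benefit, so that an interacting drug is substituted unless the benefit of concurrent use exceeds the risk. The default to substitute then holds whenever risk equals or exceeds benefit, and a medicine may be kept only when its benefit is the greater.

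The cost is one corrected sentence. It adds no patients, visits or procedures and changes nothing in the analysis.

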## **11.5 Compliance Criteria**

Treatment Duration for the first and second cycle of MCT will be considered for compliance in stage I. As the primary objective is to evaluate the disease control after the second cycle hence treatment duration on the subsequent cycles are not considered, although every effort will be made to ensure that all cycles are delivered in a timely fashion.

Per Protocol: Treatment of first 2 cycle should be completed within 8 weeks. In case of delay of any nature except due to toxicity or progression of disease if the treatment is completed within 9 weeks ( with all 8 weekly doses of methotrexate administered and not more than 6 cumulative doses of erlotinib and celecoxib missed) the patients would be considered compliant

The compliance with oral treatment will be assured by verbal confirmation from the patient and his closest caretaker .

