| Scientific Title               | “Stage I/II study of oral metronomic methotrexate with celecoxib and erlotinib as palliative chemotherapy in oral cancer patients”                                                                                                                                                                                                                                                                                                           |
| Countries of Recruitment       | India                                                                                                                                                                                                                                                                                                                                                                                                                                               |
| Health Condition Studied       | Squamous cell cancers of head and neck region warranting palliative chemotherapy                                                                                                                                                                                                                                                                                                                                                                    |
| Interventions                  | Weekly oral chemotherapy with:
De escalating dose of oral methotrexate given weekly D1 
 
1. Dose Level 0: 15 mg/m^2
 
2. Dose Level I: 12 mg/m^2
 
3. Dose Level II: 09 mg/m^2
 
4. Dose Level III: 06 mg/m^2
 
5. Dose Level IV: 03 mg/m^2
 
 Fixed dose of erlotinib 150 mg OD
Fixed dose of celecoxib 200 mg BD |
| Aim                            | Stage 1 : To identify the optimal biological effective dose (OBD) of methotrexate in combination with celecoxib ( 200 mg PO BD) and erlotinib (150 mg PO OD)

Stage 2 : To estimate the median PFS in head and neck cancer patients warranting palliative chemotherapy with the combination of celecoxib 200 mg BD, erlotinib 150 mg OD and oral weekly methotrexate                                                                          |

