### Delivery setting

The cycles may be delivered in inpatient and/or outpatient basis. Reported adverse events, potential risks and appropriate dose modifications are described in Section 13. No investigational or commercial agents or therapies other than those described below may be administered with the intent to treat the participant's malignancy.

The starting dose of methotrexate will be 15 mg/m^2. The dose of methotrexate in a given patient will remain fixed in the subsequent cycles subject to the dose modification criteria mentioned below. Dose de escalation will be done for methotrexate only as per the schedule mentioned below. Once the clinically effective and biologically optimal dose of methotrexate is discovered then this dose will be administered in subsequent stage 2 study.

| Dose Level                                                        | Dose of Methotrexate* |
|-------------------------------------------------------------------|-----------------------|
| Level 0 – Starting Dose                                           | 15 mg/m   |
| Intermediate dose level between dose level 0 & 1
(if required) | 13 mg/m   |
| Level 1                                                           | 12 mg/m   |
| Intermediate dose level between dose level 1 & 2 (if
required) | 10 mg/m   |

|                                                                |                      |
|----------------------------------------------------------------|----------------------|
| Level 2                                                        | 09 mg/m  |
| Intermediate dose level between dose level 2 & 3 (if required) | 07 mg/m  |
| Level 3                                                        | 06 mg/m  |
| Intermediate dose level between dose level 3 & 4 (if required) | 04 mg/m  |
| Level 4                                                        | 03 mg/m  |

Table 2: Dose levels of methotrexate for dose de escalation.

| Day | Agent               | Dose                                                                                               | Route                        | Schedule      |
|-----|---------------------|----------------------------------------------------------------------------------------------------|------------------------------|---------------|

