## 15 Sample size calculation

**Total sample size** : Stage 1 ( 20-30 patients) + Stage 2 ( 76 patients). In stage the continuous reassessment model will be used hence the sample size would be maximum of 30 and minimum around 20. The exact calculations done in both stages are described below in details.

Stage 1 : Flexible-finite sample based approach will be adopted to select the circulating endothelial cells (CEC) interval boundaries and further to use optimum interval design. During the trial, we will continuously update the posterior estimates of decline in CEC and clinical benefit rate and assign patients to the most appropriate dose combination (Figure 1). The Bayesian adaptive screening design will be used to simultaneously select among possible treatment dose combinations. The design is based on formulating the selection procedure as a Bayesian hypothesis testing problem in which the superiority of each treatment combination is equated to a single hypothesis. During the trial conduct, we intend to use the current values of the posterior probabilities of all hypotheses to adaptively allocate patients to treatment combinations. The dose-finding decision will be decided on the twin endpoints the clinical benefit rate at 2 months and proportional decline in CEC at D8 of first cycle. Figure 2 will be used for decision making.

Stage 2: It was assumed that the 3-month progression-free survival (PFS) rate of a standard cancer therapy is 0.50 (H0). An improvement to 0.60 would be considered clinically significant (H1). Assume both the null and alternative PFS distributions follow an exponential distribution. The 1-sided type I error rate of 0.05 and type II error rate of 0.1. Prior assumption includes a fixed enrollment rate of 3 patients per month. We require a stop of 3 months at the end of Stage 1. The library("OptInterim") has been used to calculate the sample size. A 20%extra patient would be taken to account for lost to follow up data. Hence **a total of 76 ( 63 patients +13 patient) sample size is found suitable to carry out the study for stage II with single arm drug therapy.**

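### Stage 1 per-protocol compliance is a count of single doses, but Section 11.5 names only verbal confirmation to measure it

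*Protocol*

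**What the plan says.** Protocol Section 11.5 sets the compliance window: "Treatment Duration for the first and second cycle of MCT will be considered for compliance in stage I". It gives as the reason that disease control is judged after the second cycle.

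The per-protocol rule has two parts. Treatment is expected to finish in 8 weeks; that sentence carries no dose count. The second part is an allowance for delay: "In case of delay of any nature except due to toxicity or progression of disease if the treatment is completed within 9 weeks", and there the count appears in parentheses: "with all 8 weekly doses of methotrexate administered and not more than 6 cumulative doses of erlotinib and celecoxib missed". The section closes with the method of measurement: "The compliance with oral treatment will be assured by verbal confirmation from the patient and his closest caretaker".

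Other sections bear on the point as follows.

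- Section 11.2, Table 2, sets the main methotrexate levels at 15, 12, 9, 6 and 3 mg/m2, with optional intermediate levels of 13, 10, 7 and 4 mg/m2. Table 3 places methotrexate on days 1, 8, 15 and 22 of each 4-week cycle.
- Section 12.2 plans nine plasma methotrexate draws over 30 hours, in Stage 1 only, at cycle 1 day 1.
- Section 15 bases the dose decision on the "twin endpoints the clinical benefit rate at 2 months and proportional decline in CEC at D8 of first cycle".
- Section 25 gives 6 patients for each of 5 levels, 30 at most.

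**The concern.** The rule turns on single doses: one missed methotrexate tablet day is enough to fail it. Treatment is oral and can be given to outpatients, and the only named evidence is what the patient and caretaker say. Nothing in the text secures a record of whether doses 2 to 8 were taken, or taken in full.

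Two things depend on that record. One is the per-protocol label itself. The other is the reading of 2-month clinical benefit by dose level, one of the two endpoints that select the methotrexate dose carried into Stage 2. If delivered dose drifts below assigned dose and nobody knows by how much, a weak result at one level cannot be separated from under-dosing at that level. Home intake cannot be reconstructed later.

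**Working it through.** **1. The plan's own figure.** Table 3 gives 4 methotrexate days per cycle. Over 2 cycles, 4 x 2 = 8 doses. This agrees with the 8 in Section 11.5.

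**2. What is observed objectively.** Plasma sampling covers cycle 1 day 1, so 1 of 8 doses. The study calendar (Section 13) schedules visits at cycle 1 days 1 and 8 and at day 1 of the early cycles. Of the 8 doses, 5 fall between scheduled visits: cycle 1 days 15 and 22, and cycle 2 days 8, 15 and 22.

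**3. Is there another intake check?**

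- Section 17 lists a baseline form and toxicity proformas; none is described as capturing intake.
- Section 19 has two staff verify the drug before each cycle, which checks supply, not ingestion.
- Section 11.3 refers to documentation duties for the participant and to a treatment record for breaks, but describes no intake document and no source for the entries.

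**4. Size of a missed dose.** With k of 8 doses missed, mean delivered dose = assigned dose x (8 - k) / 8.

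| Assigned (mg/m2) | k = 1 | k = 2 |
|---|---|---|
| 15 | 13.1 | 11.25 |
| 12 | 10.5 | 9.0 |

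One miss at 15 mg/m2 comes close to the optional 13 mg/m2 level. Two take the patient below Level 1. Two misses at 12 mg/m2 land exactly on Level 2.

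**5. Size of a dose step in missed doses.** Equivalent misses = 8 x (higher - lower) / higher.

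- 15 to 12: 8 x 3/15 = 1.6
- 12 to 9: 8 x 3/12 = 2.0
- 9 to 6: 8 x 3/9 = 2.7
- 6 to 3: 8 x 3/6 = 4.0

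A single miss is therefore smaller than any main step, and the issue is sharpest at the upper levels.

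**6. Short doses.** Section 11.2 rounds down to 2.5 mg tablets. The protocol gives no body surface area, so 1.5 m2 is an assumption. At that value 15 mg/m2 is 22.5 mg (9 tablets), and 12 mg/m2 is 18 mg, rounded to 17.5 mg (7 tablets). Over an assumed range of 1.3 to 1.8 m2 the two levels differ by 1 or 2 tablets per week. Confirming that the dose was taken does not by itself confirm the number of tablets.

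**7. How much could go unreported?** The protocol gives no accuracy for verbal report. Let s be the assumed chance that any one miss is reported, with misses independent. The chance that none of k misses is reported is (1 - s)^k.

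| s | k = 1 | k = 2 |
|---|---|---|
| 0.3 | 0.70 | 0.49 |
| 0.5 | 0.50 | 0.25 |
| 0.7 | 0.30 | 0.09 |
| 0.9 | 0.10 | 0.01 |

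The answer depends almost wholly on s.

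**8. Weight of one patient.** With 6 patients at a level, each contributes 1/6 = 16.7 percentage points to that level's observed clinical benefit rate.

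**The case against.** The strongest reply is that report by the patient, backed by a caretaker, is a legitimate method, and that crossing a main dose level takes at least two missed weekly doses which neither of them mentions. Much of this stands, and it limits what can be claimed.

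- A reader might infer that verbal report cannot detect misses of this size. The documents do not support that. They give no accuracy for it, and two misses both go unreported with a chance anywhere from 0.49 to 0.01 over the assumed range. Nor do they show that errors would run towards over-reporting. What they show is that no objective check is specified.
- A reader might also take the allowance of 6 missed erlotinib or celecoxib doses as evidence about dose levels. It is not. Section 11.2 de-escalates methotrexate only, so the allowance bears on the compliance label alone.
- The dose count stands in the 9-week clause. Its use for patients who finish in 8 weeks is implied, not written.
- The day 8 endothelial cell endpoint follows essentially one methotrexate dose, and that dose has plasma sampling.
- No section says that the compliance label removes a patient from the dose decision. A tablet count would not undo missed doses; it would show how many there were.
- The case report form and proformas sit in appendices that are not in the text available, so an intake field there cannot be ruled out.

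What remains is that Section 11.5 itself fixes the method, and the method it fixes is verbal only.

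**Conclusion.** The point holds as a low-cost improvement, not as an error that invalidates Stage 1. The protocol defines per-protocol compliance by counting doses and names no objective way to count them after the first methotrexate dose. At the upper levels, one or two unrecorded misses out of eight shift the mean delivered dose by about one optional or one main level. The consequence falls mainly on the compliance label and on interpreting 2-month clinical benefit by level, where about 6 patients per level leave little room for misclassification.

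This rests on the text of Section 11.5 as the full statement of the method, on equal weekly doses, and on 6 patients per level, which the adaptive allocation may change. How often misses would go unrecorded is unknown, and no effect on the selected dose has been quantified. No sample size figure changes.

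**What to change.** In Section 11.5:

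1. Add a count of returned tablets or blisters at cycle 1 day 8 and at the start of each cycle. The count at the start of cycle 3 closes the two-cycle window.
2. Add a simple diary recording the date and number of methotrexate tablets taken. The date matters because Section 11.2 allows a missed methotrexate dose to be taken up to two days late.
3. Define compliance from the count and diary, with verbal confirmation as a supplement.
4. State whether the dose count applies to all Stage 1 patients, including those who finish within 8 weeks.
5. Report delivered methotrexate dose by level alongside the clinical benefit results.

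The visits are already in the study calendar. The cost is a few minutes of coordinator time per visit and one line on the case report form. Tablet counts are imperfect too, since a tablet not returned is not proof that it was swallowed. No dose, schedule or sample size is altered.
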